### Sample size calculation

The sample size was determined using a procedure of 1000 simulations. Based on own preliminary results and previously reported prevalence, the prevalence of HCC in our screening population was set at 12% [17–19]. Secondly, the sensitivity and specificity of the SMS protocol was assumed be 80% and 72%, respectively, based on our own data analysis [15]. For US, the sensitivity and specificity were assumed to be 53% and 91%, respectively [8, 15]. Then, the number of true and false positives and true and false negatives were generated. Using exact binomial testing, the *p*-value from comparing US and SMS was obtained. Next, this procedure was repeated by generating 1000 datasets and investigating the proportion of samples with *p*-value below 0.05 (α-level). Finally, the sample size was determined by setting the power (1-β) at 80%. This resulted in a calculated sample size of 470 assuming a drop-out rate of 10–15%.

Furthermore, given the dynamic enrollment of the participants, we estimated that the average number of screenings will be 2.5 per patients. Using the calculated sample size, the total number of screenings over the study period will be 1,175 screenings of paired US-SMS. In addition, similar prospective studies have been carried out with comparable numbers [18, 19]. Therefore, our study cohort will have a sufficient sample size to evaluate the value of the SMS and relate to other similar studies.

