### Surveillance program

Patients enrolled into the study receive paired US-SMS surveillance with a 6-month interval, with an inclusion period of 3 years. The US surveillance will be performed by radiologists or hepatologists with at least 3 years of experience with US of the liver and upper abdomen on current clinical applied ultrasound systems. Participating centers have different brands of US systems with a model build 0.5 to 6 years ago. Reading of the US will be done by one reader who will also evaluate the SMS as one of three readers.

MRI will be performed on clinical applied 1.5-T system from different vendors using a dedicated body coil with an 8–16 channel range. The SMS will consist of three sequence parameters as specified in Table 2. Each SMS will be evaluated by three experienced and well-trained radiologists who will be blinded for each other’s findings and of which two readers will also be blinded for US findings.

**Table 2 Tab2:** Scan parameters of the short MRI surveillance (SMS) protocol on 1.5-T systems

Sequence	Matrix size	Slice thickness (mm)	Gap (mm)	Repetition time (ms)	Echo time (ms)	Flip angle (°)	Duration (min:s)
Axial, T1-weighted 3D gradient-echo in-out phase	300 × 260	4	0	6.2	2.1/4.2	12	0:16
Axial, T2-weighted fast spin-echo with fat saturation	320 × 320	6	0.5	Dependent on triggering	93.8	160	3:42 (dependent on respiratory frequency)
Axial, echo-planar diffusion-weighted (*b* = 50, 100, and 800 s/mm^2^)	120 × 150	6	0.6	Dependent on triggering	60.1	90	2:34 (dependent of respiratory frequency)

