### Imaging criteria for suspicious HCC lesions and confirmation

On US surveillance, a suspicious nodule is defined as follows:A nodule larger than 1 cm, previously not seen or increased in size compared to previous US;A nodule without typical features of simple cysts or hemangiomas;Impression of diffuse infiltrative lesion(s) with or without portal vein obstruction;Occurrence of thrombosis in previously patent portal or hepatic vein.

Reporting will be done according to LI-RADS US algorithm for visualization score and detection category of lesions.

With the SMS, a suspicious nodule is defined as a newly appearing or enlarging nodule that shows at least one of the following imaging features:Hypointensity on T1-weighted imaging;Hyperintensity on T2-weighted imaging;Restricted diffusivity;Nodule-in-nodule pattern (mosaic appearance);Nodule with heterogeneous fatty changes;Nodule containing blood products.

Diffuse infiltrative lesions with or without a suspected (tumor) thrombus or a new thrombus in the portal- or hepatic vein without distinct lesions will be also considered suspicious. Reporting of the SMS will be done first by quality assessment of SMS acquisition and secondly by detection category of lesions. Observations will be related to previous SMS, if available. Consensus will be reached on interpretation and registration of findings on SMS by majority vote.

In case of suspicious findings on the US or SMS, a full liver MRI protocol examination will be scheduled within 2 weeks, adopting the protocol as described by Willemssen et al. [15]. The protocol will consist of the SMS sequences and, additionally, a coronal and axial T2-weighted single-shot fast-spin echo; an axial, dynamic phase, 3D gradient echo T1-weighted image with fat suppression; contrast-enhanced axial dynamic phase, 3D gradient echo T1-weighted images with fat suppression; and a coronal, gradient echo T1-weighted image with auto calibrating reconstruction for cartesian sampling. Contrast-enhancement will be done using 7.5 cc gadobutrol 1 mmol/mL at a rate of 2 mL/sec and a saline flush of 30 mL.

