## Discussion

The aim of this study protocol is to evaluate the value of the SMS and compare it to the current standard of biannual US surveillance for HCC. This is a prospective multicenter study with a paired design for a single arm of patients.

Previous studies have proven the value of HCC imaging surveillance with US when compared to no screening [22, 23]. Jespen et al. [24] suggested that it may be necessary to perform more randomized controlled trials on HCC surveillance to determine whether the benefits of surveillance weigh up against the harms and the costs. A large scale randomized controlled trial showed that semiannual screening with US reduced HCC-related mortality by 37% for those who underwent surveillance, despite suboptimal adherence to the surveillance program (58.2%) [23]. Other studies have reinforced the benefits of surveillance in high-risk patients with detection of more early-stage HCC with consequently a higher rate of curative treatments and better survival than in the non-surveillance group [25, 26]. Kim et al. [27] and An et al. [28] have published study protocols based on abbreviated ncMRI protocols. Either the patients were offered an annual screening using ncMRI or were assigned to biannual US surveillance with a cross-over study design of biannual ncMRI surveillance or US [27, 28]. We believe that our study design of paired US-SMS will allow for a direct head-to-head comparison in diagnostics and patient acceptance.

To the best of our knowledge, this is the first published paired US-MRI study design. We expect that the proposed SMS will detect at least twice as many early-stage HCC lesions and be the next step in improving the hepatitis-cirrhosis HCC care chain. Based on our preliminary results and emerging insights from the literature, we expect the projected cost-effectiveness analysis to favor SMS [13–15]. We also expect the SMS to improve sensitivity for detection of early-stage HCC as an objective surveillance imaging tool, compared to US and may gain patient acceptance as a new standard for imaging surveillance of HCC.

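### The stated blinding does not keep the ultrasound reading free of study MRI findings, so the ultrasound accuracy estimates can be MRI-informed, above all in repeat rounds

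*Protocol article*

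**What the plan says.** The aim given in the Discussion is to "evaluate the value of the SMS and compare it to the current standard of biannual US surveillance for HCC".

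The arrangements that bear on the independence of the two tests are these:

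- **Rounds** (Surveillance program): "Patients enrolled into the study receive paired US-SMS surveillance with a 6-month interval, with an inclusion period of 3 years".
- **Who scans** (Surveillance program): "The US surveillance will be performed by radiologists or hepatologists with at least 3 years of experience".
- **Who reads US** (Surveillance program): "Reading of the US will be done by one reader who will also evaluate the SMS as one of three readers".
- **Blinding** (Surveillance program): the SMS readers are "blinded for each other’s findings and of which two readers will also be blinded for US findings".
- **Use of prior images** (Imaging criteria): one US criterion is a nodule over 1 cm that was "previously not seen or increased in size compared to previous US". SMS observations are related to the previous SMS where there is one.
- **Work-up** (Imaging criteria): a suspicious finding on either test leads to a full liver MRI, or to CT where MRI is undesirable. The result is reported by LI-RADS and discussed at the centre's tumour board.
- **Number of rounds** (Sample size calculation): "we estimated that the average number of screenings will be 2.5 per patients", so that "the total number of screenings over the study period will be 1,175 screenings of paired US-SMS".

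**The concern.** The protocol takes care to protect SMS from US: two of its three readers do not know the US result. It states no matching protection of US from SMS. It also gives the US reading to someone who reads SMS, a task that includes looking at the previous SMS. Under the text as written, a US result can be recorded by a person who knows study MRI findings that ordinary US surveillance would not have produced.

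Such knowledge can act in two ways. A nodule already judged benign on MRI may be dismissed on US, which raises US specificity. A location flagged on MRI may be searched harder, which raises US sensitivity. Either way the US figures would look better than those of US alone. SMS would then be compared with something other than the current standard, and the US pathway of the cost-effectiveness model would inherit the wrong accuracy.

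This differs from the US reader's vote in the SMS majority decision, where information flows from US to SMS. Removing that vote would not by itself keep earlier MRI findings from whoever performs or reads the US.

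**Working it through.** **1. Share of screenings that can follow an earlier study SMS.** Inputs from Sample size calculation: 470 patients and 2.5 screenings per patient on average.

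- Plan's total: 470 × 2.5 = 1,175, which reproduces.
- First rounds: 470, if every patient has one.
- Repeat rounds: 1,175 − 470 = 705, and 705 / 1,175 = 60%.

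This is before drop-out. It counts rounds in which an earlier SMS exists, not rounds in which the US reader is known to have seen it.

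**2. How many HCC-free patients would be sent for full MRI after round 1.** Inputs from Sample size calculation: specificity 72% for SMS and 91% for US, hence false-positive rates of 28% and 9%. The joint distribution is not given, so two cases are shown.

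- False positives nested (every US false positive is also an SMS false positive): 28%.
- False positives independent: 1 − 0.72 × 0.91 = 1 − 0.655 = 34.5%.

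**3. How much of that is due to SMS.** A suspicious US triggers full MRI by itself, so 9% would have one anyway.

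- Nested: 28 − 9 = 19 points.
- Independent: 34.5 − 9 = 25.5 points.

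**4. Sensitivity to the SMS specificity.** The Background reports 72–91% for the pilot. At the upper end:

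- Nested: 9%, an excess of 9 − 9 = 0 points.
- Independent: 1 − 0.91 × 0.91 = 17.2%, an excess of 17.2 − 9 = 8.2 points.

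**5. Which accuracy measure is exposed.** An HCC flagged by SMS in one round goes to full MRI within two weeks and then to the tumour board, so it would normally be diagnosed before the next US. Across rounds, what remains is mostly lesions cleared as benign, which bear on specificity, and lesions left indeterminate. A substantial gain in US sensitivity would need the SMS to be known in the same round, and the document does not say whether it is.

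**The case against.** **This is a condensed article.** Reading order and access to prior images may be set in the full protocol, and the design flowchart is not reproduced in the text at hand. That stands for the order within a round. The wording even hints that US comes first, since the third SMS reader is the one not blinded to US. It does not dispose of the point: one-directional blinding and the shared reader are stated design, not omitted detail.

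**Performer and reader may differ.** A hepatologist may scan, and the document does not say that the same person reads a given patient in every round. This stands. The exposure is something the plan permits, not something it establishes for every examination.

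**US positivity is anchored to the previous US.** This limits the dismissal of a nodule that is new on US, but it sets a size reference and is not blinding. Another US criterion depends on whether a nodule looks like a simple cyst or haemangioma, a judgement that a known MRI can sway.

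**The bias works against SMS.** Better-looking US would not create a false claim of SMS superiority. That is true and lowers the stakes, but it does not help the estimates of US accuracy or the cost-effectiveness model.

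**Stronger readings that the document does not support.** A reader might infer that from round 2 on the comparator simply is MRI-informed US. The document does not show that each US examiner sees the MRI. A reader might also infer that about a third of round-2 US examinations follow a known contrast MRI only because of the study. That ignores the 9 points due to US itself and the CT alternative, takes the lowest pilot specificity, and assumes that a result discussed at the tumour board reaches the US examiner. Finally, a reader might convert the exposure into lost power. The document gives no rate at which SMS-only cancers would become US-positive, and across rounds most such cancers would already be diagnosed, so any power figure would rest on an invented input.

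**Conclusion.** The point holds in a limited form. The plan shields most of the SMS reading from US but states nothing that shields US from study MRI, and it names a reader common to both. The US result can therefore be MRI-informed: possibly in the same round, and in up to 60% of screenings (705 of 1,175) through earlier SMS or full MRI.

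Among HCC-free patients, SMS adds about 19 to 25 percentage points to full-MRI referrals after round 1, on the plan's 72% and 91% specificities and with false positives between nested and independent. At 91% SMS specificity the addition is 0 to 8 points. These figures measure opportunity for carry-over, not bias. The likely effect in repeat rounds is on US specificity and on indeterminate lesions, and its size cannot be derived from the document.

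It deserves correction because the paired head-to-head comparison is the purpose of the study, and a US reading made with MRI knowledge cannot be undone later.

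**What to change.** Add to Surveillance program and Statistical analysis:

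1. The US result used in the accuracy comparison is recorded and time-stamped before that round's SMS is opened, is judged against earlier US only, and is not revised after MRI has been seen.
2. Any MRI-informed addendum to the US report serves care and stays out of the accuracy analysis.
3. A round-1-only comparison of SMS and US is pre-specified as a sensitivity analysis. A time-stamp cannot remove a reader's memory of earlier MRI, and round 1 is the only round without earlier study MRI. It is free of study MRI only if item 1 also fixes the order within the round.

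**Cost.** The round-1 analysis uses data already collected but has fewer events and lower precision: 470 of 1,175 screenings, or 40%, with the share of cancers found in that round not given. The time-stamp is a small workflow burden at six centres. The article describes Castor forms for the SMS readers only, so a US entry may have to be added. Setting earlier MRI aside when judging a real-time examination is also not a trivial request in clinical surveillance, which is why the addendum is kept and the round-1 analysis is needed.

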### Imaging criteria for suspicious HCC lesions and confirmation

On US surveillance, a suspicious nodule is defined as follows:A nodule larger than 1 cm, previously not seen or increased in size compared to previous US;A nodule without typical features of simple cysts or hemangiomas;Impression of diffuse infiltrative lesion(s) with or without portal vein obstruction;Occurrence of thrombosis in previously patent portal or hepatic vein.

Reporting will be done according to LI-RADS US algorithm for visualization score and detection category of lesions.

With the SMS, a suspicious nodule is defined as a newly appearing or enlarging nodule that shows at least one of the following imaging features:Hypointensity on T1-weighted imaging;Hyperintensity on T2-weighted imaging;Restricted diffusivity;Nodule-in-nodule pattern (mosaic appearance);Nodule with heterogeneous fatty changes;Nodule containing blood products.

Diffuse infiltrative lesions with or without a suspected (tumor) thrombus or a new thrombus in the portal- or hepatic vein without distinct lesions will be also considered suspicious. Reporting of the SMS will be done first by quality assessment of SMS acquisition and secondly by detection category of lesions. Observations will be related to previous SMS, if available. Consensus will be reached on interpretation and registration of findings on SMS by majority vote.

In case of suspicious findings on the US or SMS, a full liver MRI protocol examination will be scheduled within 2 weeks, adopting the protocol as described by Willemssen et al. [15]. The protocol will consist of the SMS sequences and, additionally, a coronal and axial T2-weighted single-shot fast-spin echo; an axial, dynamic phase, 3D gradient echo T1-weighted image with fat suppression; contrast-enhanced axial dynamic phase, 3D gradient echo T1-weighted images with fat suppression; and a coronal, gradient echo T1-weighted image with auto calibrating reconstruction for cartesian sampling. Contrast-enhancement will be done using 7.5 cc gadobutrol 1 mmol/mL at a rate of 2 mL/sec and a saline flush of 30 mL.

In the case of undesirable full liver MRI protocol examination, then multiphase CT scan of the liver will be offered to the patient. At minimum, 64-row multidetector CT scanners from different vendors will be used. The protocol will consist of a non-contrast, late arterial, portal-venous and equilibrium phase with standard technical parameters as described by Kulkarni et al. [20]. Full MRI or multiphase CT will be evaluated and reported conform LI-RADS and discussed within the multidisciplinary liver tumor board of the respective centers for confirmation on the final diagnosis and recommendations for clinical management.

### Endpoints

The primary endpoint of this study is the sensitivity, specificity, the positive predictive value, and an estimated negative predictive value for early-stage HCC detection by SMS with respect to US surveillance during a 3-year follow-up.

A secondary endpoint is the cost-effectiveness of SMS compared to US surveillance. It is hypothesized that despite the direct higher costs of MRI, SMS will be cost-effective. We expect that SMS will detect at least twice more early-stage HCC than US, based on calculated sensitivity and specificity of the pilot study [15]. This may allow for relative less expensive treatment with favorable patient outcome when compared with specialized liver surgery and chemotherapy regimes in case of more advanced stage HCC [21]. These differences in management and inherent costs will be addressed within the calculations of the cost-effectiveness study.

Another secondary endpoint of this study is the patient acceptance of the SMS as the potential new screening standard modality. Patients will be invited to circumvent their experiences, through a questionnaire which also allows to express their compliance with both modalities.

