## Methods

### Study design

The study protocol was reviewed and approved by the Medical Ethics Review Committee (MEC-2022-0731). Written informed consent will be signed and obtained from all participating patients by the investigators. This trial is registered at the international trial registry of ClinicalTrials.gov (NCT05429190).

This is a prospective, multicenter, observational patient cohort study. Patients will be recruited from the already existing US surveillance cohorts of six hospitals in the Netherlands. Patients will be invited for paired US-SMS surveillance, every 6 months (Fig. 2).

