### Patient recruitment and selection

The inclusion of patients will be done at (1) the Erasmus Medical Center Rotterdam; (2) the Amsterdam University Medical Center; (3) the St. Franciscus Gasthuis & Vlietland, Rotterdam; (4) the Maasstad hospital, Rotterdam; (5) the Albert Schweitzer hospital, Dordrecht; and (6) the Medisch Spectrum Twente, Enschede. The inclusion and exclusion criteria are based on the recommendations from the guidelines database from the Royal Dutch Medical Association [16] (Table 1).

**Table 1 Tab1:** Inclusion and exclusion criteria

Inclusion criteria	Exclusion criteria
- Patients age ≥ 18 years at time of enrollment - Patients diagnosed with chronic hepatitis B ◦ All patients diagnosed with chronic hepatitis B and liver cirrhosis ◦ The following patients diagnosed with chronic hepatitis B without liver cirrhosis: ▪ East-Asian men ≥ 40 years of age ▪ East-Asian women ≥ 50 years of age ▪ Patients from sub-Saharan Africa ≥ 20 years of age ▪ Patients with HCC family history - Patients diagnosed with non-hepatitis B cirrhosis: ◦ Patients diagnosed with hepatitis C ◦ Patients diagnosed with alcoholic cirrhosis ◦ Patients diagnosed with hemochromatosis ◦ Patients diagnosed with primary biliary cirrhosis	- Patients age < 18 years at time of enrollment - Patients who decline to sign the written informed consent form - Patients with contraindications for undergoing magnetic resonance imaging examination

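### Acceptance of SMS and compliance are read from a questionnaire to MRI-eligible consenters, so for the whole surveillance population they are likely, though not provably, overstated

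*Protocol article*

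**What the plan says.** In the protocol article, the Endpoints section lists acceptance among the secondary endpoints: "Another secondary endpoint of this study is the patient acceptance of the SMS as the potential new screening standard modality". Patients report their experience "through a questionnaire which also allows to express their compliance with both modalities". No other source for compliance is named there.

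The respondents are defined elsewhere in the Methods:

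- Study design gives the source population: "Patients will be recruited from the already existing US surveillance cohorts of six hospitals in the Netherlands". It also gives what they are asked to undergo: "Patients will be invited for paired US-SMS surveillance, every 6 months".
- Table 1, under Patient recruitment and selection, lists two relevant exclusions: "Patients who decline to sign the written informed consent form" and "Patients with contraindications for undergoing magnetic resonance imaging examination".

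The Discussion presents the paired design as a head-to-head comparison that includes patient acceptance. It expects that SMS "may gain patient acceptance as a new standard for imaging surveillance of HCC".

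**The concern.** The endpoint is worded as acceptance of a possible new standard, which is a question about everyone who would be offered SMS in place of US. The answers come only from patients who can have MRI and have agreed to repeated MRI. Two of the entry conditions act specifically on SMS. A patient who declines because of the MRI leaves before the questionnaire is given, and so does a patient who cannot have MRI. Neither appears in the result.

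For compliance, the named measure is what patients say about themselves, although each surveillance round either takes place or does not and can be counted. The Discussion cites 58.2% adherence in a large randomised trial of semiannual US. That figure says nothing about selection in this study, but it shows that the authors regard actual adherence as relevant to the value of surveillance.

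At stake is how far a favourable questionnaire result can support SMS as a standard. The accuracy comparison does not depend on it.

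**Working it through.** **No figure to reproduce.** The article gives no acceptance rate, target, consent rate or contraindication rate. The size of any bias therefore cannot be derived from it, and only bounds under assumed inputs are possible.

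**Inputs (all assumed).** *a* = 0.90, acceptance among participants; *u* = 0.60 or 0.80, share of invited MRI-eligible patients who consent; *b* = acceptance of SMS among those who decline, unknown, between 0 and 1.

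**Formula.** Acceptance among all invited eligible patients is *A* = *u·a* + (1 − *u*)·*b*.

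| *u* | *u·a* (if *b* = 0) | *u·a* + (1 − *u*) (if *b* = 1) | Range of *A* |
|---|---|---|---|
| 0.60 | 0.60 × 0.90 = 0.54 | 0.54 + 0.40 = 0.94 | 54–94% |
| 0.80 | 0.80 × 0.90 = 0.72 | 0.72 + 0.20 = 0.92 | 72–92% |

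**Direction.** The questionnaire figure exceeds *A* by *a* − *A* = (1 − *u*)(*a* − *b*).

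- At *u* = 0.60 this runs from 0.40 × 0.90 = 36 points too high (*b* = 0) to 0.40 × 0.10 = 4 points too low (*b* = 1).
- At *u* = 0.80 it runs from 0.20 × 0.90 = 18 points too high to 0.20 × 0.10 = 2 points too low.

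The observed 90% lies inside both ranges. It is an overstatement only if decliners accept SMS less often than participants (*b* < *a*). That is plausible, because some will decline on account of the MRI, but nothing in the article shows it.

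**Contraindication is a separate step.** If a share *c* of surveillance patients cannot have MRI, and uptake among the eligible is *U*, uptake of SMS in the whole surveillance population is (1 − *c*)·*U*. This step can only lower population uptake, but it reflects eligibility and not rejection of SMS. It belongs in its own line and should not be counted as non-acceptance. The article gives no value for *c*.

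**Compliance.** The Endpoints section names self-report. The Sample size calculation section plans 470 patients with on average 2.5 screenings each, 470 × 2.5 = 1,175 paired screenings. The Data storage and management section has SMS readers entering their findings in an electronic report form. Completed SMS examinations per round should thus be countable from data the study already collects, and US examinations are part of the same schedule. A direct measure is within reach.

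**The case against.** The strongest reply is that the article claims little. It plans a questionnaire about patients' experience, promises no population acceptance rate, and says only that SMS may gain acceptance. Each participant experiences both tests, so the within-patient comparison is sound for those studied. That stands.

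Several further points also stand:

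- Consenting to a study is not the same as accepting a test after repeated experience of it. A participant may still prefer US or drop out; the sample size allows for 10–15% drop-out.
- Patients consent to US plus SMS. Some may decline because of the double examination or the research burden and would accept SMS alone. The paired burden could also lower measured compliance.
- Recruiting from US surveillance cohorts is not a flaw. That is the population in which SMS would replace US, and if it favours either test it may favour US.
- Excluding non-consenters and patients who cannot have MRI is unavoidable in a paired MRI study.
- A screening log and attendance fields may be in the full protocol, which is not shown. Their absence from the article is not an error.

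Two things remain. The endpoint is worded for a new screening standard, and pairing cannot recover patients who never entered. And the one measure the article does name for compliance is self-report, which is a stated choice rather than an omitted detail.

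**Conclusion.** The questionnaire gives a valid comparison of SMS with US among MRI-eligible patients who consented to paired surveillance. For the whole surveillance population, acceptance and uptake are likely overstated. This rests on the assumption that decliners accept SMS less often than participants, which the article neither supports nor refutes. Under the assumed 90% acceptance, the bounds are 54–94% at 60% consent and 72–92% at 80% consent. These are illustrations and not estimates of bias.

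A reader might infer more than this. One such inference is that acceptance is high by construction and certain to be overstated; the documents do not show this, since direction depends on why patients decline. Another is that only the lower bounds, 54% and 72%, matter; those require that no decliner would accept SMS. A third is that the acceptance figure inflates the cost-effectiveness result. The Statistical analysis section describes a Markov model using centre data and literature, with sensitivity analyses, and does not say that questionnaire acceptance enters it as uptake.

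Severity is minor to moderate: a secondary endpoint, no effect on the primary accuracy analysis, and an inexpensive improvement.

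**What to change.** 1. Define compliance by recorded attendance and completed examinations per six-monthly round, separately for US and SMS, and keep the questionnaire as a supplement.
2. Count the surveillance patients approached at each site. Report those with an MRI contraindication separately as ineligible, not as non-acceptors. Count those declining and, where they volunteer a reason, note whether it was the MRI, the double examination or the research burden.
3. Report uptake with invited eligible patients as denominator, beside the questionnaire result.
4. State that the questionnaire conclusion applies to MRI-eligible consenters.

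The cost is a short count-only log at six sites and a few attendance fields, with no added visit, procedure or patients. If the full protocol already holds such a log, only the reporting rule and the definition of compliance need changing. Reasons for declining are best captured during recruitment, as they are hard to recover later. The downside is a probably lower headline figure. Attendance recorded under paired surveillance would still reflect the burden of both tests, and this should be said when it is reported.

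### Compliance with ultrasound and SMS is described only as self-reported, although the paired design lets attendance at each modality be counted directly

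*Protocol article*

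**What the plan says.** Endpoints (protocol article) states: "Another secondary endpoint of this study is the patient acceptance of the SMS as the potential new screening standard modality". Patients are invited to describe their experiences "through a questionnaire which also allows to express their compliance with both modalities". No other section says how compliance is obtained.

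Surveillance program states: "Patients enrolled into the study receive paired US-SMS surveillance with a 6-month interval, with an inclusion period of 3 years". Study design adds: "Patients will be recruited from the already existing US surveillance cohorts of six hospitals in the Netherlands". Data storage and management describes the transfer of images to a central platform and the entry of SMS readings in an electronic form.

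On expected losses, Sample size calculation says: "This resulted in a calculated sample size of 470 assuming a drop-out rate of 10–15" per cent. It gives neither the reasons for leaving nor the modality concerned.

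**The concern.** Acceptance is an attitude, and a questionnaire is the natural way to measure it. Compliance is a behaviour, and this study schedules and can observe it for both modalities in the same patient at every round. Replacing an observable fact with an invited self-report brings in recall error, a wish to please and, above all, non-response. Patients who find six-monthly MRI unsustainable may well be among those least likely to answer.

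At stake is how far the compliance result can support SMS as a new surveillance standard. The Discussion claims that the paired design permits a head-to-head comparison of patient acceptance. Counted attendance would give that claim a verifiable base; self-report gives a weaker one. The primary accuracy comparison is not affected.

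**Working it through.** **The article's own figures.** It states no compliance or acceptance rate, so there is none to reproduce. The drop-out range comes from the sample size section. As a check that drop-out acts there as an inflation factor, take the stated sensitivities of 80% (SMS) and 53% (ultrasound), prevalence 12%, power 80%, alpha 0.05 taken as two-sided, and the two tests assumed independent given HCC:

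- Discordant probabilities: 0.80 × 0.47 = 0.376 and 0.20 × 0.53 = 0.106; sum 0.482, difference 0.270.
- McNemar (asymptotic): n = (1.96√0.482 + 0.842√(0.482 − 0.270²))² / 0.270² = 49.5 patients with HCC.
- 49.5 / 0.12 = 412 evaluable patients; 412 / 0.90 = 458 and 412 / 0.85 = 485.

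The stated 470 lies between these, so it fits an allowance for patients lost within the 10–15% range. (An exact binomial test gives somewhat lower power, about 73–76% at 400–423 evaluable patients, but the present point does not depend on this.) The expected leavers number 470 × 0.10 = 47 to 470 × 0.15 = 70.5.

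**How far self-report could be off.** Assumptions:

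- c = compliance with SMS among responders, assumed 90%;
- d = drop-out, 10–15% (article);
- s = share of leavers who left because of SMS and do not answer, unknown, so varied from 0 to 1. They count as non-compliant; all other leavers are taken to comply at rate c.

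Compliance in all enrolled = c(1 − d) + c·d(1 − s). Overstatement = c − that value = c·d·s.

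| s | d = 10% | d = 15% |
|---|---|---|
| 0 | 0 | 0 |
| 25% | 2.25 points | 3.4 points |
| 50% | 4.5 points | 6.75 points |
| 100% | 9.0 points | 13.5 points |

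The ceiling scales with c: at an assumed 95% it is 0.95 × 0.10 = 9.5 to 0.95 × 0.15 = 14.25 points.

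**Per examination rather than per patient.** The table counts each SMS-related leaver as wholly non-compliant. If such leavers miss only a fraction f of their scheduled rounds, and patients have equal numbers of scheduled rounds, the overstatement is c·d·s·f. With f assumed to be one half, the ceiling of 9.0–13.5 points falls to 4.5–6.75.

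**What this leaves out.** Misreporting by responders, and non-response among patients who stay but skip SMS, are not modelled. The figures cover loss through drop-out only.

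**The case against.** The named endpoint is acceptance, not compliance. The questionnaire merely also lets patients state their compliance, which may mean little more than willingness, and nothing in the wording rules out attendance figures from study records. Completed SMS examinations should leave a trace on the imaging platform anyway. This stands, and it is why the questionnaire should be kept. It does not remove the point: the one source the article names for compliance is the weaker of two that the design makes available.

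A reader might infer that patients who stop coming are left out of the result. The article does not say so. It does not state when, how often or to whom the questionnaire is given, details that a condensed article may leave to the full protocol. A reader might also infer that SMS compliance is therefore overstated. That would require leavers not to answer and to have left because of SMS, and the documents support neither. Leaving may equally remove patients who comply poorly with ultrasound, so the direction of any bias in the comparison between modalities is not fixed.

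Two further arguments should not be used. Self-report does permit a within-patient contrast, because the same patient is asked about both modalities. And the Discussion, which describes a mortality benefit in another trial "despite suboptimal adherence to the surveillance program (58.2" per cent), neither calls adherence the limiting factor, nor says how it was measured, nor offers it as a benchmark for SMS.

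**Conclusion.** The point holds as a weakness in a stated instrument. Compliance is described only as self-report in a study that can count attendance per modality. Whether this biases the result cannot be told from the documents. Loss of leavers could overstate SMS compliance by anything from zero to about 13.5 points at an assumed 90% among responders. The upper end needs every one of the 10–15% who drop out to have left because of SMS and not to have replied, and it is smaller when examinations rather than patients are counted.

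The matter concerns one item within a secondary endpoint and is worth correcting because correction is cheap. Selection at entry is separate: recruitment comes from existing ultrasound attenders, and the exclusion list has "Patients with contraindications for undergoing magnetic resonance imaging examination". That limits how far either measure generalises, and counting attendance does not cure it.

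**What to change.** Keep the questionnaire for acceptance, experience and preference. Under Endpoints, define compliance from study records as follows:

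- For each modality, examinations completed divided by examinations scheduled, in all enrolled patients, from enrolment until HCC diagnosis, death or study end.
- For every examination, record completed, aborted or missed, with the reason where it was not completed.
- Report the within-patient ultrasound minus SMS difference with a confidence interval clustered by patient.
- Report rounds after withdrawal by stated reason, and add a sensitivity analysis that counts them as not completed. Do not assign them to one modality by default: leaving a paired study can end both study examinations without showing which was rejected.

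The cost is the wording of one endpoint and one case-report field per examination, with no extra visits or patients. The reported compliance may turn out lower, and attendance at paired study rounds will still differ from adherence to SMS alone in routine care.
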